#### Radiographic evaluation

Evaluation time point and project: X-ray: 1 day before surgery, 1 day, and 6 months after surgery; the anteroposterior and lateral position of the knee joint was examined; MRI (T1-weighted and T2-weighted images of axial, coronal and sagittal positions): 1 day before surgery, 6 months after surgery. The imaging assessment was conducted in a blinded manner, and the evaluators were not informed of the identity and grouping of the patients. Imaging evaluation should be performed without intervention.

#### Complications assessment

Postoperative complications, such as postoperative knee infection, deep venous thrombosis of the lower limbs, stiffness, and arthrofibrosis, will be recorded.

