## Aim of study

This study will recruit adult participants diagnosed with isolated longitudinal meniscus injuries confirmed through arthroscopic examination and scheduled for meniscus repair. The primary objective of this research is to assess the safety, effectiveness, and feasibility of implementing a digital rehabilitation program that incorporates computer vision and augmented reality as part of the postoperative rehabilitation process.

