## Methods

### Study design

This is a single-center, prospective, randomized controlled study. After receiving informed consent, participants will be randomly allocated into two groups: the experimental group and the control group will adopt the standardized rehabilitation protocol (Table 1). The experimental group will engage in a digital rehabilitation program that can be completed from home, whereas the control group will attend weekly physical therapy clinic sessions for exercise guidance. The flowchart of the study is shown in Fig. 1.

**Table 1 Tab1:** The standardized postoperative rehabilitation plan

Overall goal: Stage 1: 0–2 weeks: Control of swelling and symptoms after surgery, early progressive weight bearing, and ROM
Control of swelling and symptoms: (1) apply ice at least 3 times a day after surgery, 20 min each time; (2) apply the elastic bandage to compress the affected limb; (3) elevate the affected limb and lie flat on your back when sleeping and cushion a pillow with a certain thickness under the affected limb
ROM and brace use: (1) 0–60 degree fixation, early gentle knee movement under sitting position (2) heel support training, ensuring knee joint at 0 degrees
Weight bearing: The knee brace is secured in the fully extended knee position, and crutches are used to transition from no weight bearing to partial weight bearing as tolerated
Exercises: (1) sitting hamstring pull (2) ankle pump (3) quadriceps isometric training (4) straight leg elevation training (15–30 degrees) (5) hamstring isometric training
Overall goal: Stage 2:3–6 weeks: Early exercise and strength training, ROM, and partial weight bearing as tolerated
ROM and support use: (1) 3–4 weeks: 0–90-degree fixation, complete knee extension and bend to 90 degrees (2) 5–6 weeks 0–120-degree fixation, bend to 120 degrees
Weight bearing: With the knee brace fixed in the fully extended knee position, and using crutches, gradual weight bearing to full weight under tolerable conditions, and gradually remove of the crutches
Exercise: In addition to the training in the previous stage, include: (1) knee shin slide (2) supine straight leg raise 30 to 60 degrees (3) hip outreach training (4) lift heel stand (5) hip outreach (6) hip and (7) seat after knee flexion and stand
Overall goal: Stage 3: Weeks 7–12: Functional regression, gradual reduction of brace use, and restoration of total joint range of motion

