#### Experimental group

Patients will receive daily exercise plans via a software platform for 12 weeks. This software can be installed on the patients' smartphones. Once the patient initiates the digital therapy platform, the system will utilize the smartphone's camera to capture the patient's position in real time (Fig. 2). As the patient performs the physical therapy exercises, the system will provide demonstration videos, verbal and auditory feedback on the patient's exercise posture and duration. The digital platform will also record the patient's exercise frequency and duration. This data will then be transmitted to the software platform for detailed analysis by the research team.

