#### Control group

Patients will be referred to the clinic weekly for 12 weeks postoperatively, during which they will receive instructions on physical therapy exercises. Every week, patients will learn the exercises at the clinic and will then be asked to take the instruction sheet home to complete the remaining exercises.

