#### Compliance

To increase compliance, patients will receive adequate education on software usage before the start of the trial. Throughout the trial, patients will receive detailed instructions via handouts and reminders via texts and calls. Support will be provided to patients to answer questions throughout the trial. Compliance data will be monitored based on software usage data and patient attendance data in the clinic. The research team will collect data on patients' training frequency and duration to objectively assess participant compliance within the study.

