## Adverse event management

In this study, inadequate healing of the meniscus may be observed following suturing. After a 6-month postoperative MRI review and clinical evaluation, some patients may require an arthroscopic review to confirm meniscus healing. If the repair of the meniscus is unsuccessful, then partial meniscectomy will be undertaken.

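### Complication recording is not tied to the visits both arms share, although clinic contact is unequal to week 12, and failed healing is not named as a compared safety outcome

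*Protocol article*

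**What the plan says.** The Aim of study section puts safety in the primary objective: "The primary objective of this research is to assess the safety, effectiveness, and feasibility of implementing a digital rehabilitation program".

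The arms differ in how often staff see the patient. Control group: "Patients will be referred to the clinic weekly for 12 weeks postoperatively, during which they will receive instructions on physical therapy exercises". Study design, for the other arm: "The experimental group will engage in a digital rehabilitation program that can be completed from home". What the software captures in that arm is given under Experimental group: "The digital platform will also record the patient's exercise frequency and duration". No symptom or complication entry is described there.

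The follow-up schedule under Clinical knee function evaluation (weeks 2, 6, 12 and 24 after surgery) is not arm-specific. Neither is the 6-month MRI under Radiographic evaluation, which is read blind. Under Blinding method, interveners and patients are unblinded, while data collectors, analysts and outcome assessors should be blinded.

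On safety events, Complications assessment says: "Postoperative complications, such as postoperative knee infection, deep venous thrombosis of the lower limbs, stiffness, and arthrofibrosis, will be recorded". Failed healing appears elsewhere, under Adverse event management, where "inadequate healing of the meniscus may be observed following suturing". It is followed up there through the 6-month MRI and clinical evaluation.

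**The concern.** A comparison of complication rates needs events to be looked for equally in both arms. Here one arm meets clinic staff every week for 12 weeks and the other does not, and the sentence on complications does not restrict the comparison to the shared visits. An event that is mentioned at a weekly session and has resolved by the next follow-up could enter the record in control and have no route into it in the digital arm. The staff who would notice it are interveners, who know the allocation. Any resulting bias runs one way: fewer recorded events with home rehabilitation. The analysis cannot repair this later, because events that were never asked about cannot be recovered.

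A second, separate matter is failed healing. The protocol expects it and treats it as an adverse event, but neither the complications sentence nor the imaging section names it as an outcome to be compared. The failure most specific to a meniscus repair could then be managed patient by patient without appearing in the between-arm safety result.

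**Working it through.** **Scheduled in-person contacts to week 12**

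- Control: 12 weekly sessions (Control group) plus follow-up at weeks 2, 6 and 12 (Clinical knee function evaluation). The total is 12 if each follow-up coincides with a session, and 12 + 3 = 15 if none does.
- Digital: the 3 follow-up visits.
- Ratio: 12/3 = 4 to 15/3 = 5.
- After week 12 the schedule is the same in both arms (week-24 visit and 6-month MRI).

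**The plan's own figure**

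The Sample size section gives 26 per group for d = 0.8, alpha 0.05 and power 0.8. A two-sided two-sample t test gives 25.52, rounded up to 26 (power 0.807), so the figure reproduces. It is used below only as the denominator for event counts.

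**What unequal detection could do**

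The protocol gives no complication rate and no detection rate, so both are assumptions. Let the true risk p be equal in the two arms, detection be complete in control, and a fraction s of events be detected in the digital arm.

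- Expected recorded events, control: 26 × p
- Expected recorded events, digital: 26 × p × s
- Apparent risk ratio: s
- Spurious difference: p × (1 − s)

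| True risk p | Control events | Digital events at s = 90% / 75% / 50% | Spurious difference (percentage points) |
|---|---|---|---|
| 5% | 1.3 | 1.17 / 0.98 / 0.65 | 0.5 / 1.25 / 2.5 |
| 10% | 2.6 | 2.34 / 1.95 / 1.30 | 1.0 / 2.5 / 5.0 |
| 20% | 5.2 | 4.68 / 3.90 / 2.60 | 2.0 / 5.0 / 10.0 |

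With s = 100% the difference is zero. The counts are small: one event among 26 patients is 1/26 = 3.8 percentage points, so one or two unrecorded cases change how the result looks.

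**Failed healing: the sections side by side**

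- Adverse event management: expected, and looked for by 6-month MRI and clinical evaluation.
- Radiographic evaluation: gives times, views and blinded reading, but no healing outcome.
- Complications assessment: four examples, introduced as examples; healing is not one of them.

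The data would therefore be collected alike in both arms, but no section says they will be compared as a safety outcome.

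**The case against.** The strongest reply is that nothing says the weekly sessions feed the complication record. They are described as exercise instruction. If the blinded data collectors record complications, the natural source is the shared follow-up, and detection is then equal. That is a fair reading, and it is why the bias is a risk and not an established result. The text leaves the source open and does not exclude events noticed at the clinic.

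A second reply is that lasting events will be found anyway. This stands for stiffness and arthrofibrosis, which would show in the range-of-motion measurements at weeks 2, 6, 12 and 24 in both arms. Infection and deep venous thrombosis would normally bring the patient to care and be recalled at the next visit. Patients also receive "reminders via texts and calls" and question support, although the stated purpose is compliance and no enquiry about adverse events is described. The exposure is mainly to transient, mild or self-reported events.

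A reader might go further and argue that 3 contacts in 12 weeks mean detection of 3/12 = 25% in the digital arm, so that a true 10% in both arms appears as 10% against 2.5%. That requires every event to last about one week and never to be reported or recalled afterwards, which does not fit the listed complications.

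A reader might also infer that leaving out failed healing favours the digital arm. The documents do not support this. The list is open, Adverse event management already treats inadequate healing as an adverse event, both arms follow the same rehabilitation plan (Table 1), and the blinded MRI covers both. The omission has no direction.

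Finally, a journal article may leave forms and recorders to the full protocol, and interval estimates and test interpretation to the analysis plan. This is accepted, and no point is made of those details. What remains is the stated inequality in contact combined with a recording rule that does not neutralise it.

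**Conclusion.** The point holds as a risk that the plan leaves open. In-person contact to week 12 is 4 to 5 times higher in control, safety is part of the primary objective, and complication recording is not anchored to the shared visits. The between-arm comparison may therefore favour the digital arm. The stronger statement, that it does favour that arm, is not supported. The size cannot be derived from the protocol. The range of 0.5 to 10 percentage points rests wholly on an assumed true risk of 5-20%, equal in both arms, full detection in control and 50-90% detection in the digital arm. If only the shared visits are used and they ask about the whole interval, the bias should be small.

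On failed healing, the conclusion is narrower: Radiographic evaluation, Complications assessment and Adverse event management need to be reconciled so that it is clear whether this event is compared between arms.

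**What to change.** 1. Record complications in both arms with one structured checklist at the existing visits at weeks 2, 6, 12 and 24. It should ask about the whole interval since the last visit and be completed by the blinded data collector.
2. State that the between-arm comparison uses this source. List events found only at weekly clinic sessions separately.
3. Name failed healing on the blinded 6-month MRI, or repeat surgery, as a safety outcome compared between arms, and align the three sections accordingly.

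The cost is a one-page form at visits already planned and one outcome from an MRI already scheduled. The downside is some reliance on recall over the interval. Recall may still be slightly better in patients whose event was discussed at a clinic session, so the change reduces the imbalance and may not remove it entirely.

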Advanced technologies such as augmented reality and computer vision will have the potential to offer interactive digital therapy experiences [10]. Currently, the utilization of the VR system facilitates home-based rehabilitation training and increases its interactivity and enjoyment. [11–15] However, in VR, patients interact with a virtual environment that simulates real-life activities. The risk associated with this technology is that potentially dangerous situations may not be appropriately identified; however, images portrayed in both AR and virtual reality overlap with real-world images, thus allowing patients to be aware of potential dangers. [10] The incorporation of both virtual and real-world elements combined with real-time interaction and standard rehabilitation protocols can be leveraged to promote the recovery of an injured joint [15]. Telerehabilitation using technologies such as computer vision (CV) offers the potential for improving access to rehabilitation programs. The use of markerless human pose estimation based on computer vision in telerehabilitation is a promising research area, as it offers the advantage of closely monitoring movement without the need for external markers to capture motion data [16]. In our study, AR technology will utilize readily available devices such as smartphones, eliminating the need for additional hardware and providing greater convenience, while computer vision will facilitate real-time monitoring of patient movements and exercise postures.

The protocol of the digital rehabilitation program is based on the concept of accelerated rehabilitation after meniscal surgery proposed in 1996, suggesting that early postoperative weight bearing and knee range of motion (ROM) could reduce the risk of joint adhesions and muscle atrophy [5]. In recent years, accelerated rehabilitation programs for early weight bearing and active ROM after meniscus repair have shown positive results in patients with longitudinal meniscus tears [1, 2, 17]. Further research is warranted to investigate the safety and efficacy of early weight bearing and ROM training in patients who undergo complex meniscal tear repair, as the rehabilitation strategies may vary depending on tear pattern. [2, 18]

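### The safety objective covers the digital programme, but the safety outcome names no fall, exercise injury or symptom flare that interrupts training in either arm

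*Protocol article*

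**What the plan says.** The Aim of study states: "The primary objective of this research is to assess the safety, effectiveness, and feasibility of implementing a digital rehabilitation program". The safety in question is that of the programme, not of the operation.

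Two sections then deal with harm. Complications assessment says "Postoperative complications, such as postoperative knee infection, deep venous thrombosis of the lower limbs, stiffness, and arthrofibrosis, will be recorded". Adverse event management says that "inadequate healing of the meniscus may be observed following suturing" and describes what follows after the 6-month review.

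Other sections collect related information. Outcomes lists VAS, function scores and range of motion with follow-up at 2, 6, 12 and 24 weeks, and Table 2 checks for effusion at the final follow-up. Radiographic evaluation specifies "MRI (T1-weighted and T2-weighted images of axial, coronal and sagittal positions): 1 day before surgery, 6 months after surgery". The software records how often and how long patients train.

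As to setting, the experimental arm uses a "digital rehabilitation program that can be completed from home". Controls attend clinic weekly for 12 weeks and do the rest of their exercises at home from an instruction sheet.

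**The concern.** The objective asks whether the programme is safe, while the outcome is framed around the operation and the repair. A patient who falls during a home session, or is hurt doing a prescribed exercise, does not plainly have a postoperative complication. One data collector may record the event and another may not. During the 12 weeks of software delivery the rehabilitation plan in Table 1 moves through gradual removal of crutches (Stage 2) to step-downs, forward lunges and wall squats (Stage 3), so such events are conceivable in either arm.

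Two things are at stake. First, the trial could report on surgical and repair-related complications and still have little to say about harm from the exercise. Second, events that patients mention unprompted are more likely to be heard where patients are seen more often. Events not asked about at the time cannot be reliably recovered afterwards.

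**Working it through.** **Step 1. What each event would leave in the data, as the article is written.**

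| Event | Where it could appear | What would be known |
|---|---|---|
| Stiffness, arthrofibrosis | Complications assessment (named); range of motion at 2, 6, 12, 24 weeks | Covered |
| Failed repair | 6-month MRI; Adverse event management | Covered as an end state; not whether an exercise event preceded it |
| Fall without meniscal damage | Complications assessment, if the collector counts it | Not named; depends on chance reporting |
| Injury during a prescribed exercise | As above; MRI at 6 months if the meniscus is affected | Not named; no date or cause |
| Pain or effusion flare that interrupts training | VAS at visits; effusion only in Table 2 at the final follow-up; training records | A flare that resolves between visits (for example between weeks 6 and 12) can leave no trace; training records show a missed session but not why |

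The first two rows are covered. The last three are not collected in any defined way.

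**Step 2. Opportunity to report.** Over the first 12 weeks both arms share three scheduled assessments (2, 6 and 12 weeks). Controls also have weekly clinic attendance, so up to 12 further occasions to mention an event in person. The Compliance section gives patients reminders by text and call and support with questions, which narrows the difference, but nothing says that events are asked about.

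**Step 3. The plan's own numbers.** Sample size gives d = 0.8, alpha 0.05 and power 0.8, hence 26 per group, and 32 after 20% loss. A two-sided t test gives 25.52, rounded up to 26, so the figure reproduces. For loss, 26 / (1 − 0.2) = 32.5, or 33, while 26 × 1.2 = 31.2, or 32. The difference of one patient does not matter here. I use n = 26 and n = 32.

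**Step 4. What systematic collection could show.** With zero events in n patients, the one-sided 95% upper bound is 1 − 0.05^(1/n):

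- n = 26: 1 − 0.05^(1/26) = 0.109, or 10.9%
- n = 32: 1 − 0.05^(1/32) = 0.089, or 8.9%

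The article gives no event rate, so the rates below are assumptions. The chance of seeing at least one event in the digital arm is 1 − (1 − p)^n:

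| Assumed rate p | n = 26 | n = 32 |
|---|---|---|
| 1% | 23% | 28% |
| 2% | 41% | 48% |
| 5% | 74% | 81% |
| 10% | 94% | 97% |

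Power to detect an assumed 5% versus 15% between arms is about 22% (n = 26) or 26% (n = 32). Even complete capture would therefore support description, not a comparison.

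**The case against.** The strongest reply is that the text is wider than it looks, and much of that stands.

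- The list of complications opens with *such as*, so the four items are examples. A reader might infer that only surgical complications are recorded and that exercise injuries are excluded. The text does not say so; it supports only that they are not named. But the list is open within the class of postoperative complications, and whether a fall in a training session belongs to that class is left to the collector.
- A reader might infer that the listed complications have nothing to do with how rehabilitation is delivered. The Introduction contradicts this: it argues that early weight bearing and motion could reduce adhesions. Stiffness and arthrofibrosis are therefore rehabilitation-sensitive, as are range of motion and repair failure.
- A reader might take "The risk associated with this technology is that potentially dangerous situations may not be appropriately identified" as an admitted hazard of this intervention. In context the sentence is about virtual reality, and augmented reality is presented as letting patients see dangers. The trial does not set out to test that remark, and the point does not rest on it.
- A reader might infer that unsupervised home exercise is peculiar to the digital arm. It is not: controls also exercise at home, and the digital arm receives posture feedback. This is a reason for identical collection in both arms.
- A fuller protocol, not shown, could hold a general adverse-event definition. That limits the point to what the article states. The article does state a safety objective, a safety outcome and an adverse-event section, and the objective is the broader of the three.

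**Conclusion.** The point holds in limited form: the safety objective is broader than the safety outcome as defined. Surgical and repair-related safety can be described from what is planned, with partial information on rehabilitation from stiffness, arthrofibrosis, VAS, range of motion and MRI. Exercise-related safety is unsupported as written, because falls, exercise injuries and flares that interrupt training are neither named nor systematically collected, and what is reported unprompted could differ between arms. It would go too far to say that nothing can be concluded about safety.

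The bounds of 10.9% to 8.9% assume that every patient is asked and that none has an event. They measure how much a clean result could show, not the size of an error. This is a cheap improvement rather than a flaw that threatens the main comparison. It rests on the article alone and would fall away if the full protocol already defines and elicits these events in both arms.

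**What to change.** Add three event types to Complications assessment: falls, injury during a prescribed exercise, and exercise-related pain or effusion that interrupts training. Ask about them with identical fixed questions at the existing 2-, 6-, 12- and 24-week visits in both arms, covering the period since the last visit. Report them per arm with exact confidence intervals, separately from surgical complications, and present them as descriptive.

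If these events are not to be collected, limit the safety conclusion to surgical and repair-related complications.

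The cost is one sentence in the protocol and three questions on the visit form. Visits become slightly longer and there are more events to report. No extra visit is needed, and no exercise or clinical rule changes.
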